## Protocol

### Ethics statement

The design of this study (both before-and-after study as well as the randomized clinical trial) was approved by the Research Ethics Committee, School of Dentistry, University of São Paulo (approval no. 46974821.9.0000.0075), on June 1st, 2021. It was also submitted to
*The Brazilian Clinical Trials Registry*, code
RBR-523hrsx. The research protocol was written following SPIRIT
*(Standard Protocol Items: Recommendations for Interventional Trials)* guidelines.
^
30
^

The study will be divided into the following stages: (1) questionnaire validation, (2) randomized clinical trial, and (3) before-and-after study, each with their own methodology.

*Team and participants*

The allocation sequence was generated by an external professional (Dentist, PhD);

The participants enrollment and their assignment to interventions will be carried out by the main researcher ([name]).

*Questionnaire validation*

The inclusion of the research participants in this stage will be made upon a digital acceptance of a free and informed digital consent form (FICF), which will be digitally signed by the person in charge of the child (parents/guardians) and uploaded through a digital link, for this remote part of the study. This form presents the research objectives clearly, as well as the guidelines that will be provided to patients. Permission to disclose data will be part of this document, and shall ensure confidentiality of participant identity. All the participants will be informed that their participation in the study is voluntary and the participants will be informed that their anonymised data will be published.

*Before-and-after study nested within a randomized clinical trial*

For this stage, inclusion of participants in the study groups will also take place upon a digital acceptance of a free and informed digital consent form (FICF), uploaded through a digital link, and parents or guardians must mark the tick – box to consent for the remote part of the study, on behalf of the child. The parents/guardians of participants assigned to the face-to-face consultation group (G2) will also be required to sign a FICF.

In both stages (questionnaire validation and before-and-after study nested within a randomized clinical trial), in addition to the parent/guardian consent, the study will consider the age and level of understanding of the participants in the sample, whose agreement to participate will be obtained by reading a specific document, or verbally for those who cannot read and/or access the link provided. The form of acceptance will depend on the child’s maturity level, which may only be verbal, which does not necessarily require a signature, according to the Ethic Committee guidelines and approval. Children belonging to G2 (in person) and with sufficient understanding will be invited to fill out, in person, the same free and informed agreement form (FIAF) that had been sent to their parent/guardian online in stage 1, totaling two filled-out forms for G2 (
Figure 1). In this case, parents/guardians are also required to fill out an informed agreement.

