**Figure 2. f2:**
[figure not shown]
Validation of the questionnaire applied in the study.

*Before-and-after study nested within a randomized clinical trial*

The present research project will consist of a randomized, controlled, noninferiority, and blinded (examiners) clinical study, with 260 children aged 3 to 13 years in dental urgency situations. All of the participants investigated will be users of Basic Health Units, hospitals or dental clinics, residing in the municipality of Carangola, MG, Brazil. A link providing access to the Telehealth and Teledentistry Center from the University of São Paulo School of Dentistry (Nutes/FOUSP) platform will be sent to each patient after said patient makes the first contact through

*WhatsApp*
, a messaging app. All patients will be previously evaluated by a previously trained researcher in a teleconsultation (“before”), and then randomized and divided into two groups: G1, comprising 130 patients seen via a teleconsultation, and G2, comprising 130 patients seen via a teleconsultation and also in person (
Figure 3). The face-to-face evaluation (“after”) will be performed by two researchers who will be blinded to the result of the teleconsultation, who will perform anamnesis and clinical examination using a specific dental record, and who will answer whether or not the patient’s case is an urgent situation at the end of the evaluation. The dental condition motivating inclusion of the patient in the study will be treated by the researcher, and any other patient needs will be seen to by referring them to the health unit where they were registered.

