**Figure 3. f3:**
[figure not shown]
Inclusion of patients in the randomized control trial (before and after). G1, teleconsultation; G2, teleconsultation plus face-to-face consultation.

Patients in G1 and G2 will be followed up for seven and 14 days using specific instruments to assess the absence or presence of pain (Wong-Baker scale)
^
31
^ and quality of life, according to the child’s age (Child Perceptions Questionnaire, CPQ,
^
32
^ or Early Childhood Oral Health Impact Scale, ECOHIS).
^
33
^ In the case of urgencies involving teeth, a 12- and 24-month follow-up of the tooth reported in the teletriage will be carried out. The clinical criteria used to determine treatment success will be no fistula or exudate, no abscess, no painful symptoms, and no pathological mobility (
Figure 4).

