### Assignment

*Questionnaire validation*

The questionnaire will be applied to 140 participants, and reapplied to 14 randomized participants. Randomization, in blocks of four participants, will be performed using statistical software (MedCalc
^®^ 15.11, MedCalc Software, Ostend, Belgium), and the sequence generated will be distributed in sealed brown envelopes.

*Before-and-after study nested within a randomized clinical trial*

Randomization, in blocks of four patients, to assign them to one of the treatment groups, will be performed using statistical software (MedCalc
^®^ 15.11, MedCalc Software, Ostend, Belgium), and the sequence generated will be distributed in sealed brown envelopes. The envelopes must be opened immediately after the start of the teleconsultation.

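### A further signed consent is required after allocation, in the face-to-face arm (G2) only, so refusal after randomisation can be one-sided; one consent covering both allocations and all follow-up should come before the envelope is opened

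*Protocol article*

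**What the plan says.** The Ethics statement of the protocol article, in its part on the before-and-after study nested in the trial, describes two layers of consent.

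- **Both arms.** Entry is by digital acceptance of the consent form (FICF). Parents tick a box "to consent for the remote part of the study, on behalf of the child".
- **G2 only, parents.** "The parents/guardians of participants assigned to the face-to-face consultation group (G2) will also be required to sign a FICF".
- **G2 only, in person.** Children with enough understanding are invited to complete the agreement form (FIAF) again, "totaling two filled-out forms for G2". The text adds: "In this case, parents/guardians are also required to fill out an informed agreement".

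No second form is described for G1.

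On the timing of allocation, the Assignment section says: "The envelopes must be opened immediately after the start of the teleconsultation". The Research design section says that patients are first evaluated remotely "and then randomized and divided into two groups".

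On later follow-up, the Research design section says: "In the case of urgencies involving teeth, a 12- and 24-month follow-up of the tooth reported in the teletriage will be carried out". The Abstract calls this follow-up clinical, and the caption of Figure 4 names both groups.

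**The concern.** A randomised comparison is protected when every decision to take part is made before the allocation is known. Here a required consent is attached to participants who have already been assigned to G2. A G2 family that knows its allocation can still say no to part of the study, and a G1 family meets no such question. If the families who say no differ in pain, in the child's anxiety or in other respects, and are then lost, the remaining G2 children are a selected group while the G1 children are not.

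Two analyses would be affected. The Data analysis section compares the arms on change in pain, on quality of life and on missing teeth. The Sample size section takes the before-and-after sample entirely from G2, so the same loss would also select the children in whom a change of treatment decision is counted. The Research design section calls the trial noninferiority, and a distortion confined to one arm is especially unwelcome there.

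A second, smaller matter concerns scope. The only consent that the article describes for G1 is for the remote part, yet the 12- and 24-month criteria include fistula or exudate, abscess and pathological mobility, which point to an examination.

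**Working it through.** **Order of events.** The point turns on sequence, so the passages are set side by side.

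1. The first consent is given digitally by all families and is described as covering the remote part (Ethics statement).
2. The envelope is opened just after the teleconsultation starts (Assignment), or allocation follows the remote evaluation (Research design). The two places differ on the moment, but both put allocation before the face-to-face visit.
3. The further FICF is required of parents whose child is already assigned to G2 (Ethics statement). It therefore follows allocation and has no G1 counterpart.
4. The exclusion criteria remove G2 patients who fail to attend the face-to-face consultation. This second route of loss is also confined to G2. The two are distinct, because a family can attend and decline to sign; correcting the exclusion rule alone would leave the consent step in place.

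**Illustration of possible bias.** The documents give no refusal rate and no pain rate among refusers. Both are assumed here.

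- Inputs: *p* = 0.327, the planning prevalence of pain (Sample size), taken as the true rate in both arms; *d* = assumed share of G2 that refuses and is lost; *r* = assumed pain rate among refusers.
- Observed G2 rate = (*p* − *d* × *r*) / (1 − *d*).

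| *d* | Children (of 130) | *r* | Observed G2 rate | Shift |
|---|---|---|---|---|
| 0.10 | 13 | 0.10 | (0.327 − 0.010)/0.90 = 35.2% | +2.5 points |
| 0.10 | 13 | 0.60 | (0.327 − 0.060)/0.90 = 29.7% | −3.0 points |
| 0.20 | 26 | 0.10 | (0.327 − 0.020)/0.80 = 38.4% | +5.7 points |
| 0.20 | 26 | 0.60 | (0.327 − 0.120)/0.80 = 25.9% | −6.8 points |

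The Sample size section treats 15 points as the smallest difference of clinical relevance. The direction of the shift depends wholly on who refuses.

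**Illustration of power.** This uses a two-sided 5% normal-approximation test of 32.7% in G1 against 17.7% in G2, with pooled variance under the null hypothesis.

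- 130 against 130: standard error under the null = √(0.252 × 0.748 × 2/130) = 0.0539; under the alternative = √((0.327 × 0.673 + 0.177 × 0.823)/130) = 0.0530. Then (0.15 − 1.96 × 0.0539)/0.0530 ≈ 0.84, a power of 79.9%.
- 130 against 117 (10% lost from G2 only): the same formula gives 77.5%. With 20% lost (104 left) it gives 74.6%.

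The loss of power is modest. Selection is the larger concern.

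**The case against.** Several parts of the opposing case stand.

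- **A reader might infer that refusing to sign removes the child from the trial.** No passage says so. The exclusion criteria name non-attendance, not refusal. For the child's form, the G2 step repeats a form already sent online, which looks like confirmation. The article does not say whether the parents' second FICF is new or a repeat.
- **A reader might infer that G1 families never agreed to an in-person examination, so that the imbalance reverses at 12 and 24 months.** The documents do not support this. The consent form is not reproduced and Figure 1, on how the forms are applied, is not visible. That the late follow-up is in person is itself inferred from the word clinical and from the criteria, and it concerns only urgencies involving teeth.
- **A reader might take the shifts above as an estimate of bias.** They are not. The refusal and pain rates are assumed. The 32.7% is a planning prevalence, whereas all children enter with dental pain and the analysis compares change in Wong-Baker score by the Mann-Whitney test.
- **Few families may refuse.** They have sought urgent care for a child in pain, and the visit follows at once. Families in either arm may leave at any time (Confidentiality).

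These points limit the size and certainty of the concern. They do not remove it: the text makes the second parental consent a requirement, ties it to those already assigned to G2 and describes the first consent as covering only the remote part. A general right to withdraw does not ask G1 families to decide again; the G2 step does ask G2 families.

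**Conclusion.** The concern holds in a limited form. The protocol places a required consent step after randomisation in one arm only, beside a non-attendance exclusion that also applies to one arm only. This can bias the comparison of G1 with G2 and can select the before-and-after sample. That rests on the stated order of allocation and consent, and on the possibility that some G2 families who decline are not followed; the article does not settle the latter.

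The size cannot be known from the documents. It could be negligible if hardly anyone declines. The illustrated shifts show only that selective refusal of 10% to 20% would not be trivial against a 15-point difference, in either direction.

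On the 12- and 24-month follow-up, the supportable conclusion is narrower: the consent described for G1 should expressly cover it. Whether the form in use already does cannot be seen.

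**What to change.** 1. Before the envelope is opened, obtain one parental consent and one child assent from every family. It should cover the teleconsultation, the possible face-to-face consultation and the follow-up in both arms, expressly including the clinical follow-up at 12 and 24 months.
2. State that any later signature in G2 only confirms that consent and is not a condition of staying in the trial.
3. Keep a G2 family that declines the in-person part in G2, follow it at days 7 and 14 unless it withdraws from follow-up, and analyse it as randomised.

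**Cost.** The digital form must be reworded and becomes slightly longer, and an ethics amendment is needed. A few more families may decline, but they would do so before randomisation, which does not bias the comparison between arms. The Study status section reports that inclusion is still under way, so the change can serve the remaining participants. If the current form proves silent on late follow-up, G1 families already enrolled could be asked for that consent.

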**Figure 1. f1:**
[figure not shown]
Application of the FICF (free and informed consent form) to parents/guardians and FIAF (free and informed agreement form) that will be provided to the children. G1, teleconsultation; G2, teleconsultation plus face-to-face consultation.

### Confidentiality

The data collected will be stored using specific procedures to ensure the secrecy and confidentiality of the participants’ information. The access to the final trial dataset will be exclusive to the main researcher and the project supervisor. Only remote consultation platforms that have robust security standards, and that meet the regulations of the General Data Protection Law (LGPD) will be used to store the data. In addition, the research subjects will have the right to leave the study at any time, with no detriment to their care.

### Research design

*Questionnaire validation*

The parents/guardians of children with dental pain who seek care at the University of São Paulo School of Dentistry or the University of São Paulo Health Superintendence (SAU) will receive the contact information for one of the researchers, complete with a telephone number, and information about the requirements for having a remote consultation. The questionnaire will be applied to 140 participants, and reapplied to 14 randomized participants (
Figure 2). Randomization, in blocks of four participants, will be performed using freely available statistical software (
MedCalc
^®^ 15.11, MedCalc Software, Ostend, Belgium), and the sequence generated will be distributed in sealed brown envelopes. The envelope will only be opened after the patient accepts the FICF or FIAF at the time of the teleconsultation performed via Video For Health (V4H) platform, a service dedicated to digital health with a video call management functionality and aligned with the LGPD in Brazil.

**Figure 2. f2:**
[figure not shown]
Validation of the questionnaire applied in the study.

*Before-and-after study nested within a randomized clinical trial*

The present research project will consist of a randomized, controlled, noninferiority, and blinded (examiners) clinical study, with 260 children aged 3 to 13 years in dental urgency situations. All of the participants investigated will be users of Basic Health Units, hospitals or dental clinics, residing in the municipality of Carangola, MG, Brazil. A link providing access to the Telehealth and Teledentistry Center from the University of São Paulo School of Dentistry (Nutes/FOUSP) platform will be sent to each patient after said patient makes the first contact through

*WhatsApp*
, a messaging app. All patients will be previously evaluated by a previously trained researcher in a teleconsultation (“before”), and then randomized and divided into two groups: G1, comprising 130 patients seen via a teleconsultation, and G2, comprising 130 patients seen via a teleconsultation and also in person (
Figure 3). The face-to-face evaluation (“after”) will be performed by two researchers who will be blinded to the result of the teleconsultation, who will perform anamnesis and clinical examination using a specific dental record, and who will answer whether or not the patient’s case is an urgent situation at the end of the evaluation. The dental condition motivating inclusion of the patient in the study will be treated by the researcher, and any other patient needs will be seen to by referring them to the health unit where they were registered.

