### Sample size

*Sample for questionnaire validation*

The guidelines of the European Statistical System stipulate that the development and validation of instruments must follow five steps: (1) conceptualization, (2) questionnaire design, (3) questionnaire testing, (4) revision, and (5) data collection.
^
34
^ Considering that the questionnaire conceptualization and design have already been completed, our considerations will begin from the questionnaire testing step. The first step involved in instrument testing is evaluation by a panel of experts (content validation). There is a controversy in the literature regarding the recommended size for this panel, ranging from five to twenty members,
^
35
^
^,^
^
36
^ depending on their experience and qualifications. Subsequently, data collection will be carried out by applying the questionnaire (criterion validity). To this end, a sample size of at least 10 participants is recommended for each item
^
37
^; therefore, the minimum sample size of the present study will be 140 subjects. In order for the instrument to be considered reliable (test and retest), it must be able to produce similar results when applied to the same individual at different times, and by different interviewers. For this purpose, a sample size corresponding to 10% of the total “N” (i.e., 14 patients in the current version of the questionnaire) should be used.

*Sample size calculation for the RCT*

Primary outcome: the presence of dental pain in children and adolescents, considering independent samples (in this case, there is no pairing of individuals, and the interventions will be assigned to different individuals). The possibility of dropouts during the follow-up period was taken into account.

In performing the sample size calculation for independent samples, the proportion of dental pain observed in children and adolescents will be considered as 32.7%,
^
38
^ and the minimum, clinically relevant proportion difference will be 15%. Thus, considering a two-tailed test, a significance level of 0.05, and a power of 0.80, the calculation will yield a total number of 236 patients. Owing to the possibility of participant dropout during the follow-up period, 10% of this number will be added to the final sample, bringing the total number of patients required per experimental group to 130 (G Power, version 3.1.9.4).

*Sample size calculation for the before-and-after study*

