### Data analysis

*Questionnaire validation*

The kappa coefficient (k) and content validity index (CVI) will be used to quantify the degree of agreement among experts during content validation. In order to assess the reliability of the instrument, the test and retest results will be evaluated using the intra-examiner agreement test (kappa test,
*k*), which is the appropriate statistical procedure to assess the reliability of categorical and nominal variables. The criterion validity will be analyzed by comparing the results of the teleconsultation with those of the face-to-face consultation using the chi-square test (χ
^2^). The significance level will be set at 5%, and the data will be analyzed using
Jamovi and
RStudio software.

*Randomized clinical trial*

Primary outcome: pain (Wong-Baker scale); secondary outcomes: quality of life (questionnaires according to age group) and missing teeth.

The primary outcome of the randomized clinical study will be any change in pain score observed at the 7-day and 14-day follow-up timepoints compared to baseline. This outcome comprises an ordinal qualitative variable; therefore, comparison between the teleconsultation and face-to-face consultation groups will be performed using the Mann-Whitney test.

Other secondary outcomes will be evaluated, such as the impact of treatments on oral health-related quality of life, and the number of missing teeth after the 24-month follow-up period. Differences between the groups regarding the final and initial scores of the questionnaires on oral health-related quality of life, as well as the number of missing teeth, will be compared using Student’s t test or the Mann-Whitney test, depending on the type of data distribution (normal or non-normal). In addition, Poisson’s regression analysis will be performed to assess the influence of other variables on the results. The significance level will be set at 5%, and the data will be analyzed using Jamovi and RStudio software.

*Before-after study nested within an RCT*

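### The trial is labelled noninferiority but is sized and tested for a difference with no margin, so a finding of little or no difference could not establish noninferiority

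*Protocol article*

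**What the plan says.** Under Research design, the part on the before-and-after study nested within the trial calls the study a "randomized, controlled, noninferiority, and blinded (examiners) clinical study". The allocation is "G1, comprising 130 patients seen via a teleconsultation, and G2, comprising 130 patients seen via a teleconsultation and also in person". The article uses the word noninferiority nowhere else.

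Under Sample size, the calculation for the RCT starts from a pain proportion in per cent ("the proportion of dental pain observed in children and adolescents will be considered as 32.7") and a difference in per cent ("the minimum, clinically relevant proportion difference will be 15"). It proceeds "considering a two-tailed test, a significance level of 0.05, and a power of 0.80" and reports that "the calculation will yield a total number of 236 patients". For dropout, "10% of this number will be added to the final sample", which gives 130 per group. The 15% is not called a margin and has no direction.

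Under Data analysis, the primary outcome of the trial is the change in Wong-Baker score from baseline at 7 and 14 days, treated as ordinal, and "comparison between the teleconsultation and face-to-face consultation groups will be performed using the Mann-Whitney test". The level is 5%. The only confidence intervals named are for prevalence ratios in the before-and-after study, not for the randomised comparison.

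**The concern.** A noninferiority trial has to rule out that the new strategy is worse than the comparator by more than a stated amount. The null hypothesis of a difference test is that the groups do not differ. Failing to reject it shows only that the data did not separate the groups, and a small or noisy trial does that easily.

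The article states both the sizing and the primary test, and both belong to a difference trial. So this is a conflict within the text, not a detail left to an unseen analysis plan. An analysis plan that followed Sample size and Data analysis would carry the conflict forward, and one that did not would depart from the protocol.

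At stake is what the main comparison can conclude about children's pain. With the label in place and no margin, a non-significant result could be reported as support for teleconsultation alone even if it left appreciably more children in pain.

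**Working it through.** **Inputs**
- Pain proportion 0.327, difference 0.15 (read as percentage points), two-tailed 0.05, power 0.80: Sample size.
- 236 in total, so 118 per group; 236 × 1.10 = 259.6, so 260, or 130 per group: Sample size.
- Evaluable after 10% loss: 260 × 0.90 = 234, so 117 per group.
- Assumption: 32.7% is the share of G2 with pain at follow-up. The article gives it only as the proportion of dental pain observed in children and adolescents, so a range is shown below.

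**1. The plan's own figure.** For a difference test, n per group = [1.960√(2p̄(1−p̄)) + 0.842√(p₁(1−p₁)+p₂(1−p₂))]² / d².
- 32.7% against 17.7%: 130.3, so 131 per group and 262 in total.
- 32.7% against 47.7%: 166.5, so 167 per group and 334 in total.

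The stated inputs do not reproduce 236. That is a separate matter, and this point does not rest on it. What matters here is that the calculation described is for a test of zero difference and contains no margin.

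**2. How often a worse G1 would give a non-significant result.** This uses a two-sided two-proportion test with 117 per group: power ≈ Φ[(d − 1.960·SE₀)/SE₁], where SE₀ is pooled and SE₁ unpooled.
- d = 0.10 (32.7% against 42.7%): SE₀ = 0.0634, SE₁ = 0.0630. (0.10 − 0.1242)/0.0630 = −0.38, power 0.351, non-significant in 65%.
- d = 0.15 (32.7% against 47.7%): SE₀ = 0.0641, SE₁ = 0.0633. (0.15 − 0.1256)/0.0633 = 0.38, power 0.650, non-significant in 35%.
- With all 130 per group: 62% and 30%.

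**3. Power if 15 points were the margin M and true rates were equal.** n per group = (z + 0.842)² · 2p(1−p)/M², with 2 × 0.327 × 0.673 = 0.4401.
- One-sided 2.5% (z = 1.960): 153.5, so 154 per group.
- One-sided 5% (z = 1.645): 120.9, so 121 per group, 242 in total.

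Power at one-sided 2.5% = Φ(M/SE − 1.960), SE = √(0.4401/n).
- M = 0.15, n = 117: SE = 0.0613; 2.446 − 1.960 = 0.486; power 69%.
- M = 0.15, n = 130: SE = 0.0582; 2.578 − 1.960 = 0.618; power 73%.
- M = 0.10, n = 118: SE = 0.0611; 1.637 − 1.960 = −0.323; power 37%.
- Half-width of the 95% interval at n = 117: 1.960 × 0.0613 = 0.120, or 12 points.

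**4. Range over the assumed G2 rate**, same formulas, 117 per group:

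| G2 pain rate | Non-significant, G1 10 points worse | Non-significant, G1 15 points worse | Power, 15-point margin, one-sided 2.5% |
|---|---|---|---|
| 20% | 58% | 27% | 82% |
| 32.7% | 65% | 35% | 69% |
| 40% | 66% | 37% | 65% |
| 50% | 66% | 36% | 63% |

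**The case against.** **The label may be a stray word.** It occurs once, and neither Objectives nor Conclusions claims noninferiority on pain; the hypothesis in Conclusions concerns the screening decision. This stands as a reason why deleting the word may be the right repair. It does not remove the conflict.

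**15% may have been meant as the margin.** A noninferiority calculation at one-sided 5% with a 15-point margin gives 242, close to 236. But the text says two-tailed, calls 15% the minimum clinically relevant difference, and never calls it a margin. A margin on a proportion also cannot be applied to a Mann-Whitney test on ordinal score change.

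**Stronger readings that the article does not support.**
- A reader might infer that no planned result could establish noninferiority. A significant difference favouring G1 would imply it on the scale tested, so the point is limited to results of little or no difference.
- A reader might infer that the investigators intend to read p > 0.05 as not inferior. Nothing says how a non-significant result will be interpreted; the text only leaves that reading open.
- A reader might locate the fault in a two-sided primary test. Data analysis gives no sidedness for the Mann-Whitney test; the two-tailed wording belongs to the sample size. Sidedness is not the defect; the missing margin is.
- A reader might take 65% and 35% as properties of the planned analysis. They describe a two-proportion test at an assumed follow-up rate. All enrolled children have pain at entry, so that rate could differ widely. The operating characteristics of the Mann-Whitney test cannot be derived from the article.

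**Conclusion.** The point holds in this limited form. The declared design conflicts with the stated sizing and primary test, and a result of little or no difference could not establish noninferiority under the plan.

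That conclusion rests on the text alone. The figures are illustrations and depend on the binary scale, the normal approximation and the assumed G2 rate. For G2 rates of 20% to 50%, a truly 10-point-worse G1 would go undetected in 58% to 66% of trials. If 15 points were taken as the margin, power at equal 32.7% rates would be 69% to 73%, according to how many of the 130 per group are evaluable. It would reach 80% only at a lower pain rate, such as 20%, or with more patients.

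**What to change.** Choose one of two.

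**(a)** Delete the noninferiority label and state that a non-significant difference will not be read as noninferiority or equivalence. This costs a wording change.

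**(b)** Keep the label and make the plan match it:
- Reconcile the primary endpoint. Sample size and Outcomes use presence of pain; Data analysis uses ordinal change in score. Name one timepoint, 7 or 14 days.
- State a clinically justified margin for G1 minus G2 on that endpoint. Taking 15 points would need its own argument, because the plan calls that the minimum clinically relevant difference.
- Conclude noninferiority only if the upper limit of the two-sided 95% confidence interval lies below the margin.
- Restate the power for this rule.

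The cost of (b) is wording and a less favourable stated power: about 69% with 117 per group at 15 points, and about 37% with 118 per group at 10 points. Extra patients arise only if the sponsor wants 80% power. At a 15-point margin and 32.7% that means 154 − 117 = 37 more evaluable children per group, 74 in all, and more for a smaller margin.
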